### Study outcomes

The primary outcome of the study will be the variation of NB from baseline to the study ending and the incidence of hyperproteinemia or uremia causing the need to stop the study. Secondary outcomes include the variation of plasma protein levels (total proteins, albumin, prealbumin, transferrin, and RBP), expenditure energy measured by indirect calorimetry, and the incidence of gastrointestinal complications (abdominal distension, vomiting, diarrhea, and excessive gastric residue) and metabolic acidosis.

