## Methods

### Hypothesis and aims of the study

The hypotheses of this study are that (1) critically ill infants receiving a higher amount of proteins on enteral feeding will experience a higher increase on serum protein levels—total proteins, albumin, prealbumin, transferrin, and retinol binding protein (RBP)—and NB than children receiving a standard enteral diet, (2) the administration of an enriched protein and high-protein-enriched diet does not increase energy expenditure in critically ill infants, and (3) protein-enriched and high-enriched protein enteral diets are well tolerated, and mild gastrointestinal side effects and tolerable serum urea and total protein elevation are adverse events.

The corresponding objectives are (1) to analyze whether the administration of a higher amount of protein on enteral diet improves protein metabolism observed by the increase of specific serum protein levels (total proteins, albumin, prealbumin, transferrin, and RBP) and NB in critically ill infants, (2) to evaluate the effect of protein supplementation on energy expenditure in these patients, and (3) to register possible secondary effects of the administration of protein-enriched and high-enriched protein diet.

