### Study ending

The study will be ended:
after 7 days of enteral feeding.at PICU discharge.if hyperproteinemia greater than 8.5 g/dL is present.if serum urea levels exceed 80 mg/dL without evidence of renal function disturbance—in accordance with KDIGO (Kidney Disease Improving Global Outcomes) criteria—or suspected hypercatabolic state (underlying condition and negative nitrogen balance).

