### Statistical analysis

As there are no previous studies reporting expected standard deviations, we use the standardized difference of means for computing the optimal minimum number of patients to include in the trial. The calculation of the sample size was carried out with EPIDAT 3.1 software. Given a significance level of 5% (type I error), a power of 80% (complementary of the type II error), and a minimum detectable standardized difference of means of 0.9, we need 30 patients per group (Bonferroni correction included).

We will use an intention-to-treat approach. A descriptive analysis will be performed where quantitative variables will be described by their means and standard deviations or their medians and interquartile ranges, as appropriate. The quantitative ones will be summarized by their absolute and relative frequencies. Parametric and non-parametric tests will be employed for contrasting equality among groups.

Univariate and multivariate mixed models will be used in order to assess the effects size of the different diets (fixed effects) on the patients (random effects) unadjusted and adjusted by potential confounders, respectively. *P* values under 5% will be considered statistically significant.

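### The primary nitrogen balance change is measured to a study ending that varies by infant and may differ by arm, so the diets can be compared at unequal times

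*Protocol article*

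**What the plan says.** All references are to the protocol article.

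- **Study outcomes:** "The primary outcome of the study will be the variation of NB from baseline to the study ending". The same sentence adds a second primary component, "the incidence of hyperproteinemia or uremia causing the need to stop the study".
- **Study ending:** an infant's study ends after 7 days of enteral feeding, at PICU discharge, "if hyperproteinemia greater than 8.5 g/dL is present", or "if serum urea levels exceed 80 mg/dL without evidence of renal function disturbance". The urea criterion carries a further clause on "suspected hypercatabolic state (underlying condition and negative nitrogen balance").
- **Hypothesis and aims of the study:** the third hypothesis for the enriched diets is that "mild gastrointestinal side effects and tolerable serum urea and total protein elevation are adverse events".
- **Background:** intakes above 3 g/kg per day are associated with raised serum urea nitrogen and metabolic acidosis.
- **Recruitment, randomization, and study development:** blood and urine are sampled at admission and at days 1, 3 and 5–7. Feeding starts at a low rate and is stepped up every few hours towards 60–65 kcal/kg per day, or as indirect calorimetry indicates.
- **Statistical analysis:** "We will use an intention-to-treat approach". Mixed models are named with diet as fixed effect and patient as random effect. Time is not mentioned.
- **Discussion:** the serum protein changes are likewise taken from baseline to the study endpoint.

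No section ties the primary NB comparison to one of the scheduled visits.

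**The concern.** The end time is a post-randomisation event. Two of its four triggers are biochemical effects that the protocol itself connects with protein intake, and NB appears inside one of them. The time at which NB is last measured can therefore depend on the arm and on NB.

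This matters because NB is unlikely to be flat over the first week. Intake is being stepped up early on, and the Background places the largest calorie and protein deficit in the first few days. A last value at day 3 and a last value at day 7 are different quantities. If one arm contributes more early values, part of the observed contrast reflects when NB was measured and not what was fed. Randomisation balances infants at baseline but does not balance a stopping time set afterwards.

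**Working it through.** **1. The plan's own figure.** Statistical analysis gives 5% significance, 80% power, a standardised difference of 0.9 and 30 per group with Bonferroni. Sidedness and the number of comparisons are not stated; I assume two-sided tests and three pairwise comparisons, so alpha = 0.05/3. The noncentral t calculation needs 28 per group, within 2 of the stated 30. At 30 per group its power is 84.3%. The sample size is not in question.

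**2. Could the stopping triggers differ by arm?** Protein intake = energy target × protein per 100 mL ÷ energy per 100 mL (Table 1), at 60 and 65 kcal/kg per day:

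| Arm | Calculation | g/kg per day |
|---|---|---|
| SEN | 60 and 65 × 1.7/67 | 1.52–1.65 |
| PEN | 60 and 65 × 2.6/100 | 1.56–1.69 |
| HPEN | 60 and 65 × 5.1/110 | 2.78–3.01 |

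Only HPEN comes near the 3 g/kg per day that the Background links to raised urea. Urea endings may therefore concentrate in that arm.

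**3. Illustration A: attenuation of a true effect.** The documents give no stopping rates and no NB time course, so everything here is assumed:

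- NB change grows linearly to day 7.
- SEN gains g = 0.5 or 0.9 SD by day 7, and HPEN gains g + 0.9.
- A share q of HPEN ends at day 3 with 3/7 of its gain. No SEN infant ends early.

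Observed difference = (1 − q)(g + 0.9) + q(g + 0.9)(3/7) − g = 0.9 − q(4/7)(g + 0.9).

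For g = 0.5 this is 0.9 − 0.80q; for g = 0.9 it is 0.9 − 1.03q. Power is by noncentral t with 30 per arm and alpha 0.05/3.

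| q ending at day 3 | Difference seen, g = 0.5 to 0.9 (SD) | Power |
|---|---|---|
| 0% | 0.90 | 84% |
| 5% | 0.86–0.85 | 80–79% |
| 10% | 0.82–0.80 | 76–73% |
| 20% | 0.74–0.69 | 66–59% |
| 30% | 0.66–0.59 | 54–44% |

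The loss is smaller if endings come later: with 10% ending at day 5 the fraction 4/7 becomes 2/7, and power is 80–79%.

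**4. Illustration B: a difference from timing alone.** Suppose NB rises 0.3–1.0 SD between day 3 and day 7 in every arm, and 10–40% more HPEN infants end at day 3. The HPEN contrast shifts by −(rise × extra share), from −0.3 × 0.1 = −0.03 SD to −1.0 × 0.4 = −0.40 SD. With no true difference, the per-comparison error (normal approximation, alpha 0.05/3) rises from 1.67% to 1.9% at a shift of 0.05 SD, 5.3% at 0.20 and 19.9% at 0.40. Here the error favours a false conclusion against HPEN.

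**5. The urea clause.** It can be read in two ways. Suspected hypercatabolism with negative NB may be, like renal disturbance, an exception to the urea ending. Or it may be a further reason to end. NB influences the end time under both readings, but in opposite directions.

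**The case against.** Several counter-arguments have weight.

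- **Stopping events are counted.** They form the other primary component, so it would be wrong to say that infants with raised urea or protein drop out of sight. Each also has NB values up to the ending. This stands, but it does not make the NB comparison one at equal times.
- **The arm link is expected, not demonstrated.** The protocol hypothesises tolerable elevations, and at the energy target HPEN only touches 3 g/kg per day at its upper end. Nothing shows that discharge differs by arm. This stands and limits the claim to a possible systematic difference.
- **The sizes are assumed.** Illustration A puts every early ending in HPEN at day 3. The final visit is a day 5–7 window, so endings on days 5 or 6 may still fall within it. At low rates or with late endings the loss is a few points of power.
- **The mixed model could use every visit.** It could, but time is not among its stated effects, and the outcome is still defined at the study ending. An analysis plan could only override that definition.

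Three stronger readings are tempting and unsupported. A reader might infer that HPEN infants are cut off when nitrogen handling is at its worst; under the exception reading, urea endings would fall on infants not suspected of hypercatabolism. A reader might infer that the comparison is not intention to treat; the plan adopts that approach, and the fault lies in the endpoint's timing. A reader might infer that sampling certainly stops at the ending; this is plausible but not written.

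**Conclusion.** The point holds as a badly fixed endpoint, not as missing detail: the protocol does state a time for the primary NB change, and that time varies by infant and may depend on arm and on NB. The arm-related part rests on the urea and total protein triggers only. Neither the size nor the direction of the bias can be taken from the documents. Under the assumptions shown, it ranges from a few points of power to roughly half of it (84% to 44%), and timing alone could also produce an apparent difference. Because the primary comparison is affected and a repair is available from visits and models already planned, it should be corrected before results by arm are examined.

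**What to change.** 1. Define the primary NB comparison at one visit already scheduled, for example day 5–7 or day 3. The choice is open: day 5–7 shows more of the cumulative effect; day 3 is reached by more infants, since inclusion expects over 72 h of enteral nutrition, though that is only an estimate at entry.
2. Estimate it as a diet-by-visit contrast from the mixed model, using all visits and all randomised infants in their assigned arm.
3. Keep the incidence of stopping events as the other primary component.
4. State how infants who end before the chosen visit enter the analysis, and collect the samples already scheduled where the infant remains in the PICU.
5. Reconcile two sections: Study ending says the study is ended, while Protein-enriched diet safety leaves discontinuing enteral nutrition to the physician. The text should say whether the ending refers to the diet, to measurement or to both. The urea and hypercatabolic clause should be clarified. Which clinical rule applies is for the investigators.

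Cost: no change to the sample size or to any threshold. It is more than wording, however. Recruitment began in December 2016, and samples not taken after earlier endings cannot be recovered. The contrast will rest on the model's missing-data assumption for those infants. In an open-label trial the change of time point must be documented and dated before results by arm are examined.

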### Recruitment, randomization, and study development

Once an eligible patient is admitted to the PICU, written informed consent will be requested from parents or legal representative of the child by the physician responsible for the patient. They will be made aware that participation is voluntary, and they will be allowed to refuse further participation in the trial whenever they want.

After enrollment, the patient will be allocated randomly, in order of recruitment, into one of the three diet groups by using a randomized data table generated with EPIDAT 3.1 software (Servicio de Información sobre Saúde Pública de la Dirección Xeral de Saúde Pública de la Consellería de Sanidade, Xunta de Galicia, in collaboration with the Health Information and Analysis Unit of the Pan American Health Organization (PAHO-WHO)). A copy of the randomization list will be securely stored in an envelope located in a PICU working area desk drawer, which will be opened after patient enrollment in the study. Physicians, care givers, and investigators will know the allocation prior to the start of enteral feeding.

All patients will receive exclusively enteral nutrition via a nasogastric or transpyloric tube. The Standard Enteral Nutrition (SEN) group will be fed exclusively with cow’s milk–based infant formula (Nidina 1; Nestlé, Barcelona, Spain). The Protein-enriched Enteral Nutrition (PEN) group will be fed exclusively with a polymeric infant formula (Infatrini; Nutricia, Madrid, Spain). The High Protein-enriched Enteral Nutrition (HPEN) group will receive a polymeric infant formula (Infatrini; Nutricia) supplemented with 2.6 g of protein/100 mL of formula. The source of the protein supplement will be a non-hydrolyzed protein cow’s milk–based formula (Resource Protein Instant; Nestlé) (Table 1).

**Table 1 Tab1:** Composition of diets used in the study

	Protein (g)	Carbohydrate (g)	Lipids (g)	Energy (kcal)
Standard enteral nutrition	1.7	7.4	3.4	67
Protein-enriched enteral nutrition	2.6	10.3	5.4	100
High protein-enriched enteral nutrition	5.1	10.5	5.5	110

Content per 100 mL

Since this is an open-label trial, the assigned diet will be written down on the medical prescription of each patient and will be prepared by the PICU staff at their own unit, using for it the branded bottles where the different formulae are commercialized.

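### The primary safety outcome counts raised urea only when it ends an infant's study, so the count depends partly on unblinded attribution and on nitrogen balance, the efficacy outcome

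*Protocol article*

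**What the plan says.** The Study outcomes section of the protocol article gives the primary outcome two parts. The first is efficacy: "The primary outcome of the study will be the variation of NB from baseline to the study ending". The second is safety: "the incidence of hyperproteinemia or uremia causing the need to stop the study". The safety part therefore counts stops, and the Study ending section decides what a stop is.

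That section lists two laboratory criteria:

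- Total protein: "if hyperproteinemia greater than 8.5 g/dL is present". No exception is attached.
- Urea: "if serum urea levels exceed 80 mg/dL without evidence of renal function disturbance", judged by KDIGO criteria. The sentence then continues "or suspected hypercatabolic state (underlying condition and negative nitrogen balance" and closes the parenthesis.

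The section on recruitment and randomization states that the trial is open: "Physicians, care givers, and investigators will know the allocation prior to the start of enteral feeding". The same section schedules urea and total protein at admission and on days 1, 3 and 5–7. The diet safety section says that both are recorded as safety data.

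**The concern.** A primary safety outcome should be ascertained in the same way in every arm and should not depend on the efficacy result. Here, two infants with the same urea above 80 mg/dL can be classified differently. One is an event. The other is not, because renal disturbance was present or because a hypercatabolic state was suspected. Both conditions can arise after randomisation. The second is a matter of suspicion, formed by staff who know the diet, and it uses NB, the variable on which efficacy is judged. If the arms differ in how often raised urea is excused, the comparison of primary safety event rates mixes the effect of the diet with the effect of the filter.

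The wording also allows a second meaning, in which suspected hypercatabolism ends the study in its own right. The problem then moves from the safety outcome to the efficacy outcome.

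**Working it through.** **Step 1: the two readings side by side.** The last *or* in the urea criterion can attach to either of two places.

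| | Exception reading (natural) | Separate-criterion reading |
|---|---|---|
| Urea above 80 mg/dL with KDIGO renal disturbance | not a stop, not counted | not a stop, not counted |
| Urea above 80 mg/dL with suspected hypercatabolic state, no renal disturbance | not a stop, not counted | counted |
| Suspected hypercatabolic state without raised urea | no effect | ends the study, but is not a safety event |
| Where NB enters | the definition of the urea event | the time at which follow-up ends |
| Total protein above 8.5 g/dL | counted | counted |

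Under the exception reading, NB is both the efficacy outcome and one of the tests for whether raised urea counts. Under the separate-criterion reading, NB does not define the safety event, but it helps fix the study ending, which is the time at which the change in NB is measured. Total protein is unaffected under both.

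**Step 2: what the excusing does to the comparison (exception reading).** The plan gives no urea event rates, so there is no figure of its own to reproduce. Every rate below is an assumption chosen to show the mechanism.

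Let p be the true proportion with urea above 80 mg/dL and e the share of those events that is excused. Then

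counted proportion = p × (1 − e)

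counted risk ratio = true risk ratio × (1 − e_HPEN) / (1 − e_SEN)

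where SEN is the standard diet and HPEN the high-protein diet. Take assumed true rates of 10% (SEN) and 30% (HPEN): risk ratio 3.0, risk difference 20 points.

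| Excused SEN / HPEN | Counted SEN | Counted HPEN | Risk difference | Risk ratio |
|---|---|---|---|---|
| 0 / 0 | 10% | 30% | 20 points | 3.0 |
| 25% / 25% | 7.5% | 22.5% | 15 points | 3.0 |
| 50% / 50% | 5% | 15% | 10 points | 3.0 |
| 20% / 50% | 0.10 × 0.8 = 8% | 0.30 × 0.5 = 15% | 7 points | 1.9 |
| 50% / 20% | 0.10 × 0.5 = 5% | 0.30 × 0.8 = 24% | 19 points | 4.8 |

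Now suppose that the diets do not differ, with a true rate of 15% in both arms. Excusing 20% in SEN and 50% in HPEN gives 12% versus 7.5%, a risk ratio of 0.625. The reverse gives 7.5% versus 12%, a risk ratio of 1.6. Both departures from 1 come from the definition alone.

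**Step 3: which direction to expect.** The documents do not settle it. Staff who know the arm could attribute more HPEN rises to kidney or illness, which would hide harm. But the trial's first hypothesis is that more protein raises NB. If so, negative NB would be more common in SEN, more SEN events could be excused, and the HPEN excess would be exaggerated.

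**The case against.** The strongest defence is that the exceptions are an attribution rule: they remove urea rises explained by kidney dysfunction or catabolism, so that the outcome reflects the diet. KDIGO criteria are not a matter of opinion, and all urea values are recorded in any case. This stands in part. Counting only attributable events is a recognisable choice, and no data are lost. But recording the values does not change what the primary outcome counts. The attribution is also made after randomisation and, for hypercatabolism, by unblinded suspicion.

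Several stronger readings are tempting, and the documents do not support them:

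- *The rule makes the high-protein diet look safe.* That is one direction only. The trial's own hypothesis points the other way.
- *Negative NB alone excuses raised urea.* It does not. The text asks for a suspected hypercatabolic state with an underlying condition as well as negative NB, although many intensive care patients could be said to have an underlying condition.
- *The event depends on NB under either reading.* Under the separate-criterion reading, NB affects follow-up and not the event.
- *The whole safety outcome is affected.* Hyperproteinemia has no exception.
- *The 80% power is wrongly claimed for safety.* The statistical analysis section claims power only for a standardized difference of means and makes no claim for this incidence.

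It is also fair to note that the Abstract and Background call side effects a secondary objective. The Study outcomes section nevertheless places these stops in the primary outcome.

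**Conclusion.** The point holds for the urea component. On the natural reading of the ending rule, the primary safety count omits urea above 80 mg/dL when renal disturbance or suspected hypercatabolism is present. It therefore rests partly on arm-aware judgement and partly on the efficacy variable. The between-arm comparison can be biased in either direction. If the same share is excused in every arm, the risk ratio is preserved, but events are lost and the risk difference shrinks.

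The size cannot be stated, because no event rates or excusing rates are given. The factors of 0.625 and 1.6 on the risk ratio rest entirely on assumed excusing of 20% in one arm and 50% in the other. On the alternative reading, the safety event no longer involves NB, but NB helps determine when its own change is measured. The ambiguity needs resolving whichever reading was intended.

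**What to change.** Define the safety part of the primary outcome as any measured urea above 80 mg/dL or total protein above 8.5 g/dL, in all randomised infants, regardless of attributed cause and of whether the study was stopped. Report the incidence by arm with exact 95% confidence intervals. Within that count, report as sub-categories the events that ended the study, those with renal disturbance and those with suspected hypercatabolism, so that the attribution view remains visible.

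The investigators should also reconcile the Study ending and Study outcomes sections so that only one reading of the urea criterion is possible. Which stopping rule applies is theirs to decide.

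The cost is a change of wording and tabulation. The thresholds are the protocol's own, and the laboratory values are already scheduled and recorded. The downside is that some counted events will be due to illness and not to diet. Randomisation balances these between arms on average.

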### Data management

Trial data will be extracted from the medical history of the patient, registered by investigators on a data collection form, and recorded on a central database. Each patient will be identified by number of medical history and subject number, so confidentiality of the patient will be kept.

### Statistical analysis

As there are no previous studies reporting expected standard deviations, we use the standardized difference of means for computing the optimal minimum number of patients to include in the trial. The calculation of the sample size was carried out with EPIDAT 3.1 software. Given a significance level of 5% (type I error), a power of 80% (complementary of the type II error), and a minimum detectable standardized difference of means of 0.9, we need 30 patients per group (Bonferroni correction included).

We will use an intention-to-treat approach. A descriptive analysis will be performed where quantitative variables will be described by their means and standard deviations or their medians and interquartile ranges, as appropriate. The quantitative ones will be summarized by their absolute and relative frequencies. Parametric and non-parametric tests will be employed for contrasting equality among groups.

Univariate and multivariate mixed models will be used in order to assess the effects size of the different diets (fixed effects) on the patients (random effects) unadjusted and adjusted by potential confounders, respectively. *P* values under 5% will be considered statistically significant.

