**Methods:**

A multicenter prospective randomized controlled trial (RCT) will be performed in three hospitals. Patients meeting inclusion criteria will be randomly allocated to one of three enteral feeding formulae with different protein contents. Blood and urine test, nitrogen balance assessment, and energy expenditure testing by indirect calorimetry will be performed at the beginning of the nutrition regimen and at 24 h, 72 h and 5–7 days after initiation. The sample size for this trial is estimated to be 90 participants (about 30 participants in each group). The data analysis will be by intention to treat.

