Continuous enteral nutrition will be typically initiated within the first 24 h of PICU admission, by a transpyloric or nasogastric tube, at a rate of 0.5–1 mL/kg per hour, with increases of 0.5–1 mL/kg every 3–4 h, if well tolerated, to reach a caloric intake of 60–65 kcal/kg per day or as needed on the basis of resting energy expenditure measured by indirect calorimetry. There is no limit of time before the patient must be recruited as long as it is before the enteral feeding is initiated. The establishment of enteral nutrition should never be delayed by achieving enrollment.

Demographic data—gender, age, weight, height, and diagnosis on admission—will be recorded at inclusion. The risk of mortality at admission will be calculated by using pediatric scales: Pediatric Index of Mortality 2 (PIM2), Pediatric Risk of Mortality (PRISM), and Pediatric Logistic Organ Dysfunction (PELOD).

Blood concentrations of urea, creatinine, total proteins, albumin, prealbumin, transferrin, RBP levels, urinary concentration of urea in 24 h or isolated urine sample, and energy expenditure, oxygen consumption (VO_2_), and carbon dioxide production (VCO_2_) by indirect calorimetry (Datex S5 monitor, E-COVX; GE Healthcare/Datex-Ohmeda, Helsinki, Finland) will be measured at admission and at days 1, 3, and 5–7 after initiation of enteral feeding. Air leaks will be measured by using the mechanical ventilator. Calorimetry-derived data will be collected only in patients who meet all the following requirements: tracheal intubation, air leakage less than 10 %, fraction of inspired oxygen (FiO2) less than 80%, not treated with inhaled medicinal gases (nitric oxide, sevofluorane or heliox), and not connected to extracorporeal membrane oxygenation (ECMO). The collection of indirect calorimetry data will be carried out over 30 to 120 min.

NB will be calculated as nitrogen intake minus total nitrogen losses. Total nitrogen losses will include total urinary nitrogen and fecal/miscellaneous losses estimated in accordance with the World Health Organization recommendations [29]. Other blood biochemical parameters such as glucose, cholesterol, triglycerides, procalcitonin, C-reactive protein, ions, and blood gas will also be recorded.

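### The primary nitrogen-balance endpoint is a raw change from an essentially unfed baseline that is timed in two ways, and the planned analysis is not tied to baseline nitrogen balance

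*Protocol article*

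**What the plan says.** All references are to the protocol article.

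- **Study outcomes.** The efficacy part of the primary outcome is "the variation of NB from baseline to the study ending". Serum proteins and energy expenditure are secondary.
- **Statistical analysis.** Mixed models will "assess the effects size of the different diets (fixed effects) on the patients (random effects) unadjusted and adjusted by potential confounders". Parametric and non-parametric group tests are planned as well. No analysis is named as primary, the confounders are not listed, and baseline NB is not mentioned.
- **Timing in Recruitment, randomization, and study development.** Blood, urine and calorimetry measurements "will be measured at admission and at days 1, 3, and 5–7 after initiation of enteral feeding".
- **Timing in the abstract, Methods.** The same measurements "will be performed at the beginning of the nutrition regimen and at 24 h, 72 h and 5–7 days after initiation".
- **Feeding and sampling.** The recruitment section says that feeding usually begins within a day of admission and that recruitment can happen at any point before it begins. It defines NB as intake less losses and accepts either a 24-hour urine collection or a single sample. Parenteral nutrition is an exclusion criterion.

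**The concern.** Two features of the endpoint work against it.

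First, the value being subtracted is not fixed in time. Admission and the start of feeding can be hours or more apart, by an amount that differs between children. A later analysis plan cannot repair this, because it cannot change when a sample was drawn.

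Second, baseline NB is measured with little or no nitrogen intake, so it is roughly minus the losses. It may say little about NB on full feeds. Subtracting a weakly correlated value adds its variance to the outcome and removes little in return. Using the same value as a covariate lets the data decide how much of it to remove. At stake is precision in a trial of 90 children, on its primary efficacy outcome.

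**Working it through.** **Inputs.** The Statistical analysis section gives 5% significance, 80% power and "a minimum detectable standardized difference of means of 0.9, we need 30 patients per group (Bonferroni correction included". It has no SD to work from: "As there are no previous studies reporting expected standard deviations, we use the standardized difference of means". It does not say whether the 0.9 is in SDs of the change or of a single visit. The correlation r between baseline and final NB is not given, so it is varied below. Two-sided tests and three pairwise comparisons (alpha 0.05/3) are assumed.

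**The plan's own figure.** n per group = 2(z for alpha + z for power)²/d² = 2(2.394 + 0.842)²/0.9², which rounds up to 26. By noncentral t it is 28. With alpha 0.05/6 the normal approximation gives exactly 30. The stated 30 is therefore compatible with the inputs. At 30 per group and alpha 0.05/3, power is 86% (normal approximation).

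**Raw change against baseline adjustment.** Set the final SD to 1 and the baseline SD to q.

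- Variance of the change: 1 + q² − 2rq
- Variance after adjusting for baseline: 1 − r²
- Difference between the two: (q − r)², which is never negative

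So in large samples adjustment cannot lose, and the two analyses tie only when q = r.

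**Equal SDs (q = 1).** The ratio of adjusted to change variance is (1 − r²)/(2(1 − r)) = (1 + r)/2.

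| r | Change | Adjusted | Adjusted/change |
|---|---|---|---|
| 0.2 | 1.60 | 0.96 | 60% |
| 0.5 | 1.00 | 0.75 | 75% |
| 0.7 | 0.60 | 0.51 | 85% |

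Below r = 0.5 the change is also noisier than the final value alone, because 2(1 − r) exceeds 1.

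**Unequal SDs.** If the unfed baseline is half as variable as the final value (q = 0.5), the ratio the other way up, change to adjusted, is:

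- r = 0.1: 1.15/0.99 = 1.16
- r = 0.3: 0.95/0.91 = 1.04
- r = 0.5: 0.75/0.75 = 1.00

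The loss then nearly vanishes. If the baseline is the more variable one (q = 1.5), the ratio is 2.98, 2.58 and 2.33 at the same correlations.

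**What this means for power** (30 per group, alpha 0.05/3, equal SDs, one final visit, normal approximation):

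| r | Change, if 0.9 is in single-visit SDs | Adjusted, same scale |
|---|---|---|
| 0.1 | 58% | 87% |
| 0.3 | 71% | 90% |
| 0.5 | 86% | 95% |
| 0.7 | 98% | 99% |

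If 0.9 is already in SDs of the change, the change analysis has 86% power whatever r is, and adjustment raises this to 97% (r = 0.3) or 95% (r = 0.5).

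**The case against.** The best defence is that an article condenses the plan. The adjusted model includes potential confounders, and baseline NB may be among them. Covariate lists and time terms commonly sit in a fuller document, so their absence alone proves nothing. Under randomization the raw change is unbiased, and its cost depends on an unreported correlation and on the ratio of SDs. All of that stands, and it limits the point to precision. It does not remove the point: the article itself fixes the outcome as a raw change and gives two timings for the value subtracted.

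A reader might infer three stronger things that the documents do not support.

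- **That diet is the only fixed effect.** This could be true only of the unadjusted model. The same sentence plans an adjusted one.
- **That the analysis dilutes the diet effect.** If all four visits, baseline included, were outcome rows under a single diet term, a constant effect of 0.9 would average to 0.9 × 3/4 = 0.675. The article does not describe that model. With the outcome defined as a change, baseline is not an outcome row, and the expected difference in changes is not diluted in raw units. Power figures built on the four-row model would describe an analysis nobody has stated.
- **That the baseline urine already contains treatment effect.** A 24-hour collection begun at admission could run into feeding, since feeding usually begins within that day. This is only a possibility, because a single urine sample is also allowed.

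**Conclusion.** The point holds as one of precision and definition, and a correction is worthwhile. Baseline is timed in two ways, and the NB change is not linked to a baseline-adjusted analysis. With equal SDs, adjustment brings the variance to 60%, 75% or 85% of that of the change score at r = 0.2, 0.5 or 0.7. The gain is close to nothing if the baseline SD is about half the final SD and r is 0.3 to 0.5. A low r is plausible for an unfed baseline, but that is an assumption.

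This does not show bias, and it does not show that the trial is underpowered. The 0.9 may already be in SDs of the change, in which case 30 per group keeps 86% power.

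**What to change.** 1. Reconcile the abstract with the recruitment section so that there is one baseline: blood and urine completed before the first feed of the assigned formula.
2. Make the main NB comparison a mixed model of post-baseline NB (days 1, 3 and 5–7), with diet, visit, diet-by-visit and baseline NB as fixed effects and patient as random effect. Baseline is then a covariate and not an outcome row. State which visit's diet contrast is the main result, and how it relates to children whose study ends earlier.
3. Use the same model for serum proteins and, in children with valid calorimetry, for energy expenditure.

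**Cost.** The analysis change is wording only, since every variable is already collected. The baseline definition may require a shorter or spot urine sample in some children. The protocol already allows a spot sample, so feeding need not wait for it. The covariate uses one degree of freedom, which is minor with 90 patients.
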